## 11. MEASUREMENT OF EFFECT

Although response is not the primary endpoint of this trial, patients with measurable disease will be assessed by standard criteria. For the purposes of this study, patients should be evaluated at baseline, week 8, every 8 weeks thereafter, and at the off study visit (if the patient comes off study before week 8 or it has been more than 6 weeks since the last scan) with a CT with oral and IV contrast of the chest, abdomen and pelvis (or MRI if patient has contrast allergy). In addition a bone scan will be performed for prostate cancer patients at baseline and at study completion.

### 11.1 Antitumor Effect – Solid Tumors

Response and progression will be evaluated in this study using the new international criteria proposed by the revised Response Evaluation Criteria in Solid Tumors (RECIST) guideline (version 1.1) [**Appendix D**] and the immune related Response criteria (irRC) [**Appendix E**]. Clinical decisions regarding disease progression will be based on RECIST criteria. Changes in the largest diameter (unidimensional measurement) of the tumor lesions and the shortest diameter in the case of malignant lymph nodes are used in the RECIST criteria.

#### 11.1.1 Definitions

Evaluable for toxicity. All patients will be evaluable for toxicity from the time of their first treatment with Mistletoe.

Evaluable for objective response. Only those patients who have measurable disease present at baseline and have received at least one dose of therapy will be considered evaluable for response. These patients will have their response classified according to the definitions stated below.

Evaluable Non-Target Disease Response. Patients who have lesions present at baseline that are evaluable but do not meet the definitions of measurable disease and have received at least one dose of therapy will be considered evaluable for non-target disease. The response assessment is based on the presence, absence, or unequivocal progression of the lesions.

#### 11.1.2 Methods for Evaluation of Measurable Disease

All measurements should be taken and recorded in metric notation using a ruler or calipers. All baseline evaluations should be performed as closely as possible to the beginning of treatment and never more than 4 weeks before the beginning of the treatment.

The same method of assessment and the same technique should be used to characterize each identified and reported lesion at baseline and during follow-up. Imaging-based evaluation is preferred to evaluation by clinical examination unless the lesion(s) being followed cannot be imaged but are assessable by clinical exam.

Conventional CT and MRI This guideline has defined measurability of lesions on CT scan based on the assumption that CT slice thickness is 5 mm or less. If CT scans have slice thickness greater than 5 mm, the minimum size for a measurable lesion should be twice the slice thickness. MRI is also acceptable in certain situations (e.g. for body scans).

Use of MRI remains a complex issue. MRI has excellent contrast, spatial, and temporal resolution; however, there are many image acquisition variables involved in MRI, which greatly impact image quality, lesion conspicuity, and measurement. Furthermore, the availability of MRI is variable globally. As with CT, if an MRI is performed, the technical specifications of the scanning sequences used should be optimized for the evaluation of the type and site of disease. Furthermore, as with CT, the modality used at follow-up should be the same as was used at baseline and the lesions should be measured/assessed on the same pulse sequence. It is beyond the scope of the RECIST guidelines to prescribe specific MRI pulse sequence parameters for all scanners, body parts, and diseases. Ideally, the same type of scanner should be used and the image acquisition protocol should be followed as closely as possible to prior scans. Body scans should be performed with breath-hold scanning techniques, if possible.

#### 11.1.3 Duration of Response

Duration of overall response: The duration of overall response is measured from the time measurement criteria are met for CR or PR (whichever is first recorded) until the first date that recurrent or progressive disease is objectively documented (taking as reference for progressive disease the smallest measurements recorded since the treatment started).

The duration of overall CR is measured from the time measurement criteria are first met for CR until the first date that progressive disease is objectively documented.

Duration of stable disease: Stable disease is measured from the start of the treatment until the criteria for progression are met, taking as reference the smallest measurements recorded since the treatment started, including the baseline measurements.

#### 11.1.4 Progression-Free Survival (PFS)

PFS is defined as the duration of time from start of treatment to time of first documented progression of disease or death from any cause, whichever occurs first.

#### 11.1.5 Time to Progression (TTP)

TTP is defined as the time from start of treatment to the time of progression. Deaths (all cause) are censored at time of death.

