### **1.3 Exploratory Objectives**

- 1.3.1 To estimate progression-free survival (PFS) and time to progression (TTP) in patients treated with Helixor® M mistletoe extract using RECIST 1.1 and irRC.
- 1.3.2 To collect peripheral blood mononuclear cells (PBMCs), serum, and plasma to explore potential therapeutic targets, biomarkers, and predictors of treatment response (PFS and best overall response).
- 1.3.3 To assess tumor burden dynamics using exploratory circulating biomarkers in serial collections of sera and plasma at baseline and throughout treatment.
- 1.3.4 To collect pre and post-treatment whole blood to evaluate germline mutations in circulating DNA that may correlate with clinical benefit (PFS and best overall response).
- 1.3.5 To determine changes in cytokine production by peripheral blood mononuclear cells (PBMC) as indicated by interleukin 2 [IL-2], interleukin 6 [IL-6], interleukin 8 [IL-8], interleukin 12 [IL-12], and interferon- gamma [IFN-γ].

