## **5.7 Duration of Follow Up**

Patients will be followed for 28 days after completion or removal from study or until death, whichever occurs first. Patients who are discontinued from the study treatment due to a drug-related AE will be monitored for safety until the resolution of the AE to  $\leq$  grade 1 or stabilization or until initiation of a new therapy for their cancer, whichever occurs first.

Patients who have completed or discontinued from treatment should be contacted every six months to monitor overall survival. Information of other cancer therapies after discontinuation from the study treatment will be collected.

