- 8: Labs may be collected within a window of up to 3 days prior to dosing.
- 9: Radiologic evaluations (CT scan of the chest, abdomen, and pelvis or MRI if patient has contrast allergy) and tumor measurements (RECIST 1.1 and irRC) will be performed at baseline, week 8 (+/-7 days), and every 8 weeks (+/-7 days) thereafter. Off study scans only need to be completed if the off study visit occurs before the Week 8 scan; scans do not need to be repeated if one has been done within the past 6 weeks. Bone scans will also be performed if applicable.
- 10: Attempts to obtain surgical or biopsy archival tumor samples will be made for every subject who consents to the optional sample until the sample is obtained or documentation that the sample cannot be obtained. Detailed instructions for tissue collection, processing and shipment are provided in the

Protocol #: J1681, IRB00090991

Laboratory Manual.

- 11: For Cycle 1 Day 1 (50mg dose level) study procedures do not need to be repeated if they were conducted within 3 days of the pre-study evaluations.
- 12: Beyond Week 16, repeat the study assessments and evaluations detailed in Weeks 9-16 until one of the criteria from **Section 5.6** applies.
- 13: 28 days after their last dose of study drug or within 7 days prior to initiation of a new anti-cancer treatment, whichever comes first. Patients who have completed or discontinue from treatment should be contacted every six months (+/- 28 days) to monitor overall survival. Information regarding anti-cancer therapies after discontinuation from the study treatment will also be collected.

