Exploratory objectives will be to 1) to estimate PFS and TTP in patients treated with Helixor® M at MTD or maximum administered dose if no MTD is determined, and to measure tumor marker dynamics in patients receiving treatment, 2) collect peripheral blood mononuclear cells (PBMCs) and serum to explore potential therapeutic targets, biomarkers, and predictors of treatment response, 3) assess tumor burden dynamics using exploratory circulating biomarkers in serial collections of sera and plasma at baseline and throughout treatment, 4) collect pre and post-treatment whole blood to evaluate germline mutations in circulating DNA that may correlate with clinical benefit, and 5) determine changes in cytokine production by peripheral blood mononuclear cells (PBMC) as indicated by interleukin 2 [IL-2], interleukin 6 [IL-6], interleukin 8 [IL-8], interleukin 12 [IL-12], and interferon- gamma [IFN-γ]. PFS and TTP will be analyzed as time-to-event outcomes, for which we can estimate event-time distributions using the Kaplan-Meier method. PFS will be calculated as the time from start of treatment to time of progression per RECIST 1.1 and irRC or death, whichever occurs first. If the subject does not have a documented date of progression or death, PFS will be censored at the date of the last adequate assessment. Patients who start any subsequent anti-cancer therapy without a prior reported progression will be censored at the last evaluable tumor assessment prior to initiation of the subsequent anti-cancer therapy. TTP is the time from start of treatment to time of progression per RECIST 1.1 and irRC.

We will examine the correlation between potential therapeutic targets/biomarkers/predictors of treatment response and clinical endpoints. For time-to-event clinical endpoints, the potential predictors will be treated as covariates (time-varying or not) in Cox proportional-hazard models. For other clinical endpoints, we will use generalized estimating equations (GEE) to analyze the correlation between the potential predictors and clinical endpoints. Summary statistics and boxplots will be used to present the levels of potential predictors at each time point, assess tumor burden dynamics, compare pre and post-treatment germline mutations in circulating DNA, and examine the changes in cytokine production by PBMC.

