#### **13.4 Reporting and Exclusions**

13.4.1 Evaluation of toxicity – All patients will be evaluable for toxicity from the time of their first treatment with Mistletoe.

13.4.2 Evaluation of response – All patients included in the study must be assessed for response to treatment, even if there are major protocol treatment deviations or if they are ineligible. Each patient will be assigned one of the following categories: 1) complete response, 2) partial response, 3) stable disease, 4) progressive disease, 5) early death from malignant disease, 6) early death from toxicity, 7) early death because of other cause, or 9) unknown (not assessable, insufficient data). [Note: By arbitrary convention, category 9 usually designates the “unknown” status of any type of data in a clinical database.]

All of the patients who met the eligibility criteria (with the possible exception of those who received no study medication) should be included in the main analysis of the response rate. Patients in response categories 4-9 should be considered to have a treatment failure (disease progression). Thus, an incorrect treatment

schedule or drug administration does not result in exclusion from the analysis of the response rate. Precise definitions for categories 4-9 will be protocol specific.

All conclusions should be based on all eligible patients. Subanalyses may then be performed on the basis of a subset of patients, excluding those for whom major protocol deviations have been identified (e.g., early death due to other reasons, early discontinuation of treatment, major protocol violations, etc.). However, these subanalyses may not serve as the basis for drawing conclusions concerning treatment efficacy, and the reasons for excluding patients from the analysis should be clearly reported. The 95% confidence intervals should also be provided.

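### TTP is censored at the date of death, although no scans are scheduled after the off-study visit, so time when nobody looks for progression counts as progression-free

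*Protocol*

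**What the plan says.** TTP is exploratory. Objective 1.3.1 is "To estimate progression-free survival (PFS) and time to progression (TTP) in patients treated with Helixor® M mistletoe extract using RECIST 1.1 and irRC".

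- **Death rule.** Section 11.1.5 states for TTP: "Deaths (all cause) are censored at time of death". Section 13.3 repeats the definition, "TTP is the time from start of treatment to time of progression per RECIST 1.1 and irRC", and gives no censoring date of its own.
- **Imaging on treatment.** Calendar footnote 9 (section 10) says that scans "will be performed at baseline, week 8 (+/-7 days), and every 8 weeks (+/-7 days) thereafter". Footnote 12 repeats the assessments until a section 5.6 criterion ends treatment.
- **Imaging on leaving.** Section 11 adds a scan "at the off study visit (if the patient comes off study before week 8 or it has been more than 6 weeks", counted from the previous scan. Footnote 9 is worded more narrowly: it requires the off-study scan only if that visit precedes the week 8 scan, and waives a repeat within six weeks. Footnote 13 places the visit 28 days after the last dose, or shortly before a new anti-cancer treatment if that is sooner.
- **After that.** Section 5.7: "Patients who have completed or discontinued from treatment should be contacted every six months to monitor overall survival". Information on later cancer therapy is also collected, but no imaging is scheduled. Appendix D asks for an effort to document progression after stopping in patients with symptomatic deterioration, without setting a schedule.
- **PFS, for comparison.** Under section 13.3, when neither progression nor death is documented, "PFS will be censored at the date of the last adequate assessment". A further sentence there censors patients who start new therapy at the last evaluable assessment before it.

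**The concern.** Censoring at death is harmless only if progression is looked for until death. Here it is looked for on a schedule only until the off-study visit.

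Leaving without progression is built into the design. Section 5.6 lists DLT, severe hypersensitivity, unresolved toxicity, intercurrent illness, withdrawal of consent, noncompliance and investigator judgement as reasons to stop. Such a patient has almost no chance of a recorded event from the off-study visit to death, yet counts in every risk-set denominator during that time. The estimated progression hazard is diluted and the Kaplan-Meier curve is held up.

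Section 13.3 focuses these estimates on patients treated at the MTD or maximum administered dose, 16 patients by section 13.2. A few such deaths can move a curve of that size, and the error favors the drug.

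**Working it through.** The protocol states no TTP median, event count or departure rate, so there is no figure to reproduce. Three checks follow.

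**1. One patient, no new therapy.** The patient has stable disease at the week 8 scan, stops for toxicity at week 10 and dies at week 52. The off-study visit falls at week 10 + 4 = 14, which is 14 − 8 = 6 weeks after the scan. That is not more than six weeks, so neither section 11 nor footnote 9 requires a scan. Section 11.1.5 censors TTP at week 52. The last tumor assessment was at week 8, so 52 − 8 = 44 weeks without a scheduled scan count as progression-free.

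**2. Sixteen-patient illustration (invented data).** Documented progressions: 6 at week 8, 3 at week 16, 2 at week 24 and 1 at week 32. Four patients leave without progression, are last scanned at weeks 8, 8, 8 and 12, and die at weeks 30, 36, 40 and 34. Kaplan-Meier: S(t) = product of (1 − events / at risk).

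- Censored at death: S(8) = 1 − 6/16 = 0.625; S(16) = 0.625 × (1 − 3/10) = 0.4375; S(24) = 0.4375 × (1 − 2/7) = 0.3125.
- Censored at last scan: S(8) = 0.625; at risk at week 16 = 16 − 6 − 3 − 1 = 6, so S(16) = 0.625 × (1 − 3/6) = 0.3125; S(24) = 0.3125 × (1 − 2/3) = 0.104.

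The 24-week estimate is 31% against 10%. The median is 16 weeks either way.

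**3. Simulation, 20,000 patients per scenario.** From the protocol: scans every 8 weeks, and an off-study scan 4 weeks after leaving under the section 11 condition, the wording that yields more scans. Assumed, not in the documents: exponential progression with median 8 or 16 weeks; independent exponential departure with median 52, 24 or 12 weeks; exponential survival after the off-study visit with median 13, 26 or 39 weeks; no new therapy; no progression recorded after the off-study visit. Ranges are across the three survival medians.

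| True median (wk) | Median time to leaving (wk) | Leave without documented progression, die later | 24-week TTP-free, censored at death | Censored at last scan | Difference (points) |
|---|---|---|---|---|---|
| 8 | 52 | 10% | 16.2–17.4% | 11.7–11.9% | 4.3–5.7 |
| 8 | 24 | 19% | 20.9–23.5% | 11.7–11.8% | 9.1–11.8 |
| 8 | 12 | 30% | 28.1–31.5% | 10.7–10.8% | 17.4–20.7 |
| 16 | 52 | 21% | 39.7–40.6% | 34.6–35.1% | 4.6–6.0 |
| 16 | 24 | 34–35% | 43.7–46.5% | 33.1–34.3% | 9.9–12.2 |
| 16 | 12 | 50–51% | 50.8–54.3% | 31.5–32.5% | 18.8–21.8 |

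The smallest difference is 16.2 − 11.9 = 4.3 points and the largest is 54.3 − 32.5 = 21.8. The median gap from last scan to death is about 14 to 41 weeks.

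If everyone were scanned on schedule, the 24-week value would be 0.5^(24/8) = 12.5% or 0.5^(24/16) = 35.4%. The simulated values were 12.0–12.8% and 35.1–35.7%. Against the simulated fully scanned values, the rule as written is 3.8 points (16.2 − 12.4) to 18.8 points (31.5 − 12.7) too high. Last-scan censoring is at or up to about 4 points below them (31.5 against 35.4).

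Estimated medians also rise, from about 9–10 to 12–15 weeks and from about 16–17 to 24–35 weeks. They are less reliable here because the true medians fall exactly on a scan date.

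**The case against.** The strongest reply is that the protocol does more than the concern needs it to omit, and that little depends on TTP.

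- **Scans after stopping.** A reader might infer that imaging stops with the last dose. It does not: section 11 and footnote 9 provide a conditional off-study scan, and Appendix D asks for progression to be documented after symptomatic deterioration. This stands. The simulation includes the off-study scan and the bias remains. The Appendix D effort has no schedule, so it reduces the bias by an unknown amount.
- **New therapy.** The subsequent-therapy sentence in 13.3 names no endpoint and follows text that introduces PFS and TTP together. If it covers TTP, patients who start new therapy are already censored at the last scan and the bias is smaller. It also stands among the PFS rules, so its scope is unclear. Patients who die without new therapy are affected on either reading.
- **PFS.** A reader might infer that PFS already censors deaths at the last scan. It does not. Apart from the subsequent-therapy rule, death is a PFS event at its own date. The two endpoints will still treat deaths differently, as they should.
- **Section 13.4.2.** It is tempting to see a contradiction with "Patients in response categories 4-9 should be considered to have a treatment failure (disease progression"). That is a convention for the response rate. It also covers unknown status and death from other causes, so it does not define a TTP event. TTP is defined by RECIST 1.1 and irRC, and counting cancer deaths as progression would depart from that.
- **Who is affected.** Only deaths without earlier documented progression matter. A patient who leaves because of progression already has an event.
- **Importance.** TTP is exploratory and descriptive, with no test or decision tied to it. This stands and limits the weight of the point.

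**Conclusion.** The point holds. Section 11.1.5 fixes a censoring date that does not match the imaging schedule, and the resulting bias in Kaplan-Meier TTP is upward. Its direction was the same in all 18 scenarios (2 × 3 × 3).

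Its size cannot be taken from the protocol. Of 4 to 22 points at 24 weeks, the low end corresponds to about one patient in ten leaving without documented progression and dying later, and the high end to about half. These figures assume that departure is unrelated to progression, that no new therapy starts and that no progression is found after the off-study visit. They show sensitivity and do not forecast this trial's result.

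A reader might infer that the trial's main conclusions are at risk. The documents do not support that: the primary safety and MTD conclusions do not use TTP.

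**What to change.** In sections 11.1.5 and 13.3, state that patients without documented progression, including those who die, are censored for TTP at the last adequate tumor assessment. State also that the 13.3 subsequent-therapy censoring rule applies to TTP as well as PFS.

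Report TTP beside PFS, in which death remains an event. Last-scan censoring still treats a death from undocumented progression as uninformative, so TTP should not be read alone. The off-study scan conditions in section 11 and calendar footnote 9 should be reconciled, because they determine the last assessment date.

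The cost is about a sentence in each of two sections and no new data. Reported TTP becomes shorter, and its late estimates less precise because fewer patients remain at risk.

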## 12. DATA REPORTING / REGULATORY REQUIREMENTS

Adverse event lists, guidelines, and instructions for AE reporting can be found in **Section 7.0** (Adverse Events: List and Reporting Requirements).

## **12.1 Data Management**

All information will be collected on study-specific case report forms (CRFs) by study staff. These data will be reviewed for completeness and accuracy by the Principal Investigator at each site.

### Protocol Chair

The Protocol Chair is responsible for performing the following tasks:

- Coordinating, developing, submitting, and obtaining approval for the protocol as well as its subsequent amendments.
- Assuring that all participating institutions are using the correct version of the protocol.
- Taking responsibility for the overall conduct of the study at all participating institutions and for monitoring the progress of the study.
- Reviewing and ensuring reporting of Serious Adverse Events (SAE)
- Reviewing data from all sites.

### Coordinating Center

The Coordinating Center is responsible for performing the following tasks:

- Ensuring that IRB approval has been obtained at each participating site prior to the first patient registration at that site, and maintaining copies of IRB approvals from each site.
- Managing central patient registration.
- Collecting and compiling data from each site.
- Establishing procedures for documentation, reporting, and submitting of AE's and SAE's to the Protocol Chair, and all applicable parties.
- Facilitating audits by securing selected source documents and research records from participating sites for audit, or by auditing at participating sites.

